#### Data Management

Data pertaining to the study, including screening data, recruitment data, baseline information, daily *nasya karma* procedure assessments, laboratory test reports, and secondary outcome measures assessed using scales, will be comprehensively documented in case report forms within 24 hours, and electronic case report forms will be completed within 7 days. Only the study personnel, individuals delegated with the task of data entry, and the statisticians will have access to the data. The imaging data generated from fMRI will be stored in hard disks at AIMS and will undergo further analysis after completion of the study. All study documents will be securely stored for 5 years following study completion.

#### Statistical Analysis

##### Overview

The modified intention-to-treat principle will guide the analysis for all outcomes within the full analysis set. Quantitative data will be summarized using mean, SD, minimum, maximum, and median values. Enumeration data will be presented as frequency and the corresponding percentage. Intragroup comparisons will be conducted using the Student paired *t* test or Wilcoxon signed rank test for continuous variables and the chi-square test for categorical variables. Intergroup comparisons will be conducted using the independent-sample *t* test or the Mann-Whitney *U* test. Significance thresholds will be set at *P*<.05 for all 2-tailed tests.

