##### fMRI Data Analysis

The fMRI data will undergo preprocessing using either the Data Processing and Analysis for Brain Imaging or CONN toolboxes, which will encompass essential steps such as slice timing correction, realignment for motion correction, regression to remove confounding effects, normalization to a standard template, smoothing to enhance signal-to-noise ratio, detrending to remove low-frequency drifts, and filtering to focus on relevant frequency bands, aligning with established practices in the field. After data preprocessing, amplitude of low-frequency fluctuation, functional connectivity, and large-scale functional brain network analysis will be conducted to investigate the difference in neurophysiological responses between the groups. The results will be interpreted in the context of the experimental paradigm to elucidate neural correlates of the studied phenomena, providing insights into the effects of *nasya karma* on brain function. Voxels exhibiting expected time-course correlations (30-second periods) will receive high activation scores, whereas those showing no correlation or deactivation will receive lower or negative scores, respectively. MRI data analysis will use general linear models via statistical parametric mapping (SPM). fMRI data will be processed using MATLAB 2023 (MathWorks Inc).

Resting phase MRI data will be analyzed using software tools such as SPM, the CONN toolbox, and the Functional Magnetic Resonance Imaging of the Brain Software Library (Analysis Group), whereas task phase fMRI will specifically use SPM. Given the focus on group data in this study, complex patterns of brain activation will be interpreted collectively rather than individually. For voxel-based analysis, a significance threshold of *P*<.01 at the voxel level and *P*<.05 corrected for false discovery rate (FDR) at the cluster level will be applied. Connectome-based analysis will use a threshold of *P*<.05 corrected for FDR. Additionally, Pearson correlation analysis will be performed to explore potential associations between clinical outcomes and fMRI findings, examining changes in brain activity following different interventions.

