##### Correlation of Clinical Outcomes and fMRI Data

Associations between clinical measures and fMRI-derived metrics (amplitude of low-frequency fluctuation, functional connectivity, and network strength) will be assessed using partial Pearson correlations controlling for age and sex. Given the multiple regions and measures assessed, the Benjamini-Hochberg FDR correction (*q*<0.05) will be applied to adjust for multiple testing across correlations. In addition, exploratory Spearman correlations will be performed to confirm the robustness of the observed associations.

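### Between-group tests make no use of baseline as a covariate and the brain-behaviour correlations omit randomised group, which costs precision and can create false associations

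*Protocol article*

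**What the plan says.** **Between groups.** The Overview under Statistical Analysis states: "Intergroup comparisons will be conducted using the independent-sample *t* test or the Mann-Whitney *U* test". It names no covariate, and the variable tested (follow-up value or change) is not stated. The same paragraph opens by covering every outcome: "The modified intention-to-treat principle will guide the analysis for all outcomes within the full analysis set".

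**Within groups.** "Intragroup comparisons will be conducted using the Student paired *t* test or Wilcoxon signed rank test for continuous variables". All tests share one threshold: "Significance thresholds will be set at *P*<.05 for all 2-tailed tests".

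**Correlations.** The section on correlating clinical outcomes with fMRI data says that associations "will be assessed using partial Pearson correlations controlling for age and sex". The fMRI Data Analysis section also describes an unadjusted version: "Pearson correlation analysis will be performed to explore potential associations between clinical outcomes and fMRI findings, examining changes in brain activity following different interventions". Randomised group appears in neither.

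**Baseline data.** The Methods part of the Abstract and Table 1 schedule a pre-procedure scan on day 1 in both arms. The Abstract (day 1) and Secondary Outcome Measures (before the intervention) place a first assessment of the scales ahead of day 30. Table 1, as it reads, ticks clinical assessment only at day 30.

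**Imaging model.** The fMRI Data Analysis section names general linear models in SPM and an aim of comparing the groups. It states no group-level covariates.

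**The concern.** Three features of the stated analysis deserve attention.

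- The trial has 30 people per arm and plans to measure each outcome before treatment. A t or Mann-Whitney test on follow-up values discards that measurement. A t test on change uses it, but less efficiently than regression on baseline.
- Separate before-after tests in each arm sit beside the between-group tests with no stated order of importance, and the hypothesis in the Objectives section is framed as an increase over baseline. That makes it easy to conclude that nasya changed something because its arm reached significance and the control arm did not. Such a pattern does not test the difference between arms.
- If both arms are pooled in the correlations, a treatment effect on a scan measure and on a scale makes the two correlate across the 60 participants even when they are unrelated among people in the same arm. In a mechanistic study this could be reported as a brain-behaviour link.

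**Working it through.** **Inputs from the protocol.** 30 per group (Sample Size); d = 0.6 (Power Analysis); two-sided .05 (Overview). **Assumed:** the correlation r between baseline and follow-up, which the document does not give, so a range is shown.

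**The plan's own power figure.** The Power Analysis section claims more than 80% at voxel P<.001 with cluster-level FWE of .05. A two-sample noncentral t calculation for d = 0.6 and 30 per group gives 62.8% at two-sided .05 and 14.1% at two-sided .001. The claim is therefore not reproduced at voxel or region level. Cluster-level power cannot be recomputed, because smoothness, search volume and pilot variance are not given. That is a separate matter; here 62.8% is only the starting point.

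**Step 1: power of three between-group analyses.**

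- Follow-up only: noncentrality 0.6 × √(30/2) = 2.32, with 58 degrees of freedom.
- Change score: effective d = 0.6/√(2(1−r)), giving 0.507, 0.600 and 0.775 for r = 0.3, 0.5 and 0.7.
- Baseline-adjusted: effective d = 0.6/√(1−r²), giving 0.629, 0.693 and 0.840, with 57 degrees of freedom.

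| Assumed r | Follow-up t test | Change-score t test | Baseline-adjusted |
|---|---|---|---|
| 0.3 | 62.8% | 48.9% | 66.8% |
| 0.5 | 62.8% | 62.8% | 75.1% |
| 0.7 | 62.8% | 83.9% | 89.2% |

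Adjustment gains about 4, 12 and 26 points over the follow-up test, and about 18, 12 and 5 points over the change-score test. It is the best of the three at each r shown.

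**Step 2: reading the within-arm tests against each other.** Suppose both arms truly change by the same amount and each paired test has power p. The chance that nasya alone is significant is p(1−p). For a standardised change of 0.2, 0.3, 0.4 and 0.5, p is 0.185, 0.355, 0.563 and 0.754, so the chance is 15%, 23%, 25% and 19%.

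**Step 3: correlations with group left out.** Suppose nasya shifts each of two measures by d within-arm SDs and the two are unrelated within arms. With equal arms pooled, r = (d²/4)/(1 + d²/4).

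- d = 0.6: 0.09/1.09 = 0.083.
- d = 1.0: 0.25/1.25 = 0.20.

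By Fisher's z with n = 60 and two covariates, the standard error is 1/√(60−2−3) = 0.135. The rejection rate at two-sided .05 is about 9% for d = 0.6 and 32% for d = 1.0. A simulation of 20,000 trials without the age and sex covariates gave 9.7% and 34.2%. With group included, it gave about 5% in both cases. These are rates per test, before FDR correction.

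**The case against.** **The unadjusted test is not wrong.** A reader might infer that chance baseline differences bias the comparison. They do not: under randomisation the t test is valid and its standard error already allows for chance imbalance. The loss is one of precision.

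**The largest gain is not established.** One might also infer a loss of 26 points of power. That needs r = 0.7 and a follow-up-only test, and the Overview does not say whether follow-up or change is tested. Against a change score at the same r the gain is about 5 points. Moreover, d = 0.6 was set for fMRI activation, and the limitations section says the study is not powered for clinical efficacy.

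**The imaging model may already adjust.** The SPM general linear model can carry a baseline map or covariates, so the document does not show that the voxelwise primary analysis is unadjusted. The point is firmest for the scales and for extracted imaging measures.

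**Within-group tests cannot all be demoted.** The immediate response is one of the two components of the primary outcome, and only the nasya arm has the day-1 post-procedure scan. A within-group test is the only one available there. Nor does the document say that effects will be inferred from one arm being significant and the other not, since between-group tests are planned as well.

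**Pooling is not stated.** The correlation section does not say whether the arms are combined. The sentence in the fMRI Data Analysis section about changes after different interventions suggests it without settling it. The planned Benjamini-Hochberg correction does not remove the artefact, because the pooled correlation is truly non-zero.

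**Paired categorical data.** The chi-square test named for within-group categorical variables ignores pairing. However, no categorical outcome is defined, so nothing follows from this.

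**Left to the analysis plan?** Detail may well be. But the article names tests that admit no covariate, and lists the correlation covariates with group absent. Those are stated choices.

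**Conclusion.** The point holds as a matter of precision and interpretation, not of invalid testing. Replacing the stated between-group tests with a baseline-adjusted model raises power at d = 0.6 to 67%, 75% or 89% for assumed r of 0.3, 0.5 or 0.7. This compares with 63% for follow-up values and 49%, 63% or 84% for change scores. The size rests on the assumed r and on carrying over an effect size set for imaging. Age and sex probably add little in healthy adults aged 20 to 40 described as matched on both; most of the gain comes from baseline.

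For the correlations, omitting group matters if the arms are pooled. The effect is modest at 0.6 SD (about 9% against 5% per test) and substantial at 1.0 SD (about 32%). The higher figure needs shifts well above the protocol's own effect size.

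**What to change.** (a) **Group differences.** For the clinical scales and extracted imaging measures, estimate the day-14 or day-30 difference with a linear model on group plus baseline value, with age and sex optional, and report a 95% CI. For voxelwise maps, state that the group-level model either compares day-14-minus-baseline maps between groups or carries the baseline map as a covariate.

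(b) **Within-group tests.** Where both arms are measured (day 14, day 30), base conclusions on the between-group estimate and treat within-group tests as descriptive. Keep the within-group test of the immediate day-1 response, labelled as an uncontrolled pre-post comparison.

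(c) **Correlations.** Add group to age and sex in the partial correlations, use change scores, and also report the correlations within the nasya arm.

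(d) **Clinical baseline.** Reconcile Table 1, which ticks clinical assessment only at day 30, with the Abstract and Secondary Outcome Measures. The adjustment for the scales depends on a baseline actually being collected.

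The cost is analysis wording. No new data are needed, provided the clinical baseline is collected as the text describes.

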**Methods:**

A total of 60 healthy volunteers in the age group of 20 to 40 years who fulfill the selection criteria will be recruited for this randomized controlled trial at the National Ayurveda Institute for Panchakarma, Cheruthuruthy, Kerala, India, and randomized in a 1:1 ratio to either the intervention group (n=30; group 1, receiving *nasya karma* with *anu taila*, an oil-based formulation manufactured using a paste and decoction of herbal medicines with oils as the base material, for a period of 14 days) or the control group (n=30; group 2, not receiving any intervention). The participants will undergo task-based and resting fMRI on day 1 (twice on day 1 before administration and 15 minutes after *nasya karma* for participants in group 1) and day 14 to map the neurophysiological response to *nasya karma* of the brain. A comprehensive neuroimaging protocol using structural magnetic resonance imaging and fMRI will be used in the study. The effect of *nasya karma* on sleep, psychological well-being, cognition, and quality of life will be assessed on the 1st and 30th days in both groups.

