##### Power Analysis

A priori power analysis was conducted using G*Power (version 3.1) and the fMRIPower toolbox. On the basis of pilot data and prior studies of similar paradigms, an expected effect size of Cohen *d*=0.6 (moderate) was used. For a voxel-level threshold of *P*<.001, uncorrected and cluster-level FWE of *P*<.05, and a sample size of 30 per group, the analysis achieves >80% power to detect activation differences in relevant cortical regions. This power analysis informed our sample size and statistical thresholds.

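### The between-group test named in the Statistical Analysis Overview makes no use of the planned baseline values; it is valid but less precise than an ANCOVA on the same data

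*Protocol article*

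**What the plan says.** The Overview under Statistical Analysis gives the between-group method in one sentence: "Intergroup comparisons will be conducted using the independent-sample" *t* test or the Mann-Whitney *U* test. It names no covariate and does not say whether the values compared are follow-up values or changes from baseline. The sentence before it deals with change within each arm: "Intragroup comparisons will be conducted using the Student paired" *t* test or the Wilcoxon signed rank test, which requires a baseline value for each participant. The significance rule reads: "Significance thresholds will be set at *P*<.05 for all 2-tailed tests".

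Baseline data are planned in several places:
- **Scales, abstract (Methods):** these outcomes "will be assessed on the 1st and 30th days in both groups".
- **Scales, Secondary Outcome Measures:** an assessment before the intervention is listed, followed by days 1 and 30.
- **fMRI, Table 1:** both arms are scanned on day 1 and day 14.
- **fMRI, Preparatory Phase:** controls have resting-state mapping on the same two days.

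The only covariate adjustment the article names is in the correlation analysis, which uses "partial Pearson correlations controlling for age and sex".

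**The concern.** The comparison between randomized arms is the part of this trial that can support a causal statement. As written, the plan uses baseline values in the uncontrolled within-arm tests and states no use of them in the controlled comparison.

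The Overview sentence can be read in two ways, and each loses something. A test on follow-up values ignores the baseline. A test on changes subtracts the whole baseline value whatever its correlation with follow-up, which adds noise when that correlation is modest. ANCOVA weights the baseline by its observed correlation, so apart from a small cost in degrees of freedom it is at least as precise as either. With 30 per arm, and a Sample Size section that describes further recruitment as difficult, precision available from data already planned is worth having.

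**Working it through.** **Inputs from the protocol article.** 30 per arm; two-sided .05 (Overview); d=0.6 (Power Analysis: "an expected effect size of Cohen *d*=0.6 (moderate) was used"). That effect size was stated for imaging activation. No effect size is given for the scales, so d=0.6 serves here only as an illustration.

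**Assumed.** The correlation rho between baseline and follow-up is not in the document; 0.3 to 0.7 is shown. The SD is taken as equal at both times and in both arms.

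**The plan's own figure.** Power Analysis says that with "a sample size of 30 per group, the analysis achieves >80% power to detect activation differences in relevant cortical regions". A single two-sample *t* test with d=0.6 and 30 per arm gives 62.8% at two-sided .05 and 14.2% at two-sided .001, so the stated figure is not reproduced this way. Cluster-level power cannot be rebuilt because no cluster or smoothness inputs are given. That is a separate matter, and nothing below depends on it.

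**Formulas.** Let v be the variance of the analysed quantity relative to a single follow-up value. The noncentrality is 0.6 / sqrt(v × 2/30), and power comes from the noncentral *t* distribution.
- Follow-up only: v = 1, 58 df. Noncentrality 0.6 / sqrt(2/30) = 2.324; critical value 2.002; power 62.8%.
- Change score: v = 2(1 − rho), 58 df.
- ANCOVA with one baseline term: v = (1 − rho²) × 57/56, 57 df. The factor 57/56 = 1.018 is the expected variance cost of estimating one slope with N=60.

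| rho | Follow-up only | Change: v, noncentrality | Change: power | ANCOVA: v, noncentrality | ANCOVA: power |
|---|---|---|---|---|---|
| 0.3 | 62.8% | 1.40, 1.964 | 48.9% | 0.926, 2.415 | 66% |
| 0.5 | 62.8% | 1.00, 2.324 | 62.8% | 0.763, 2.660 | 74% |
| 0.6 | 62.8% | 0.80, 2.598 | 72.4% | 0.651, 2.879 | 81% |
| 0.7 | 62.8% | 0.60, 3.000 | 83.9% | 0.519, 3.225 | 89% |

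Without the 57/56 factor the ANCOVA column is 66.8%, 75.1%, 81.5% and 89.2%, so the cost is less than one point throughout.

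**Sample-size equivalent.** At rho=0.5, 30 / (1 − 0.25) = 40 per arm with follow-up values alone, or about 39 after the 57/56 factor.

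**Break-even.** ANCOVA beats follow-up values alone when (1 − rho²) × 57/56 < 1, that is rho > sqrt(1/57) = 0.13. With three covariates the factor is 57/54 = 1.056.

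**The case against.** The strongest reply is that this is a matter of efficiency and not an error. Randomization makes the unadjusted test unbiased and keeps its type I error, and its standard error already allows for chance baseline imbalance. The trial is exploratory and says it is not powered for clinical efficacy. All of that stands. A reader might infer that the planned comparison is biased or invalid; the documents do not support that.

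A second objection concerns reach. A reader might take the Overview's scope statement to mean that the primary imaging outcome is also tested with a bare *t* test. The sentence is: "The modified intention-to-treat principle will guide the analysis for all outcomes within the full analysis set". There, the reference to all outcomes qualifies the modified intention-to-treat principle, not the choice of test. The fMRI Data Analysis section assigns imaging to general linear models in SPM, whose group-level design the article does not give and which could carry a baseline term. It is therefore not shown that the imaging comparison is unadjusted. The point falls mainly on the secondary scales.

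A third objection is that the baseline data are less settled than the abstract suggests. Table 1 ticks clinical assessment on day 30 only, which conflicts with the abstract and with Secondary Outcome Measures. The Preparatory Phase mentions only resting-state mapping for controls, whereas the abstract has participants undergoing both task and resting scans. This also stands, and it means the remedy has preconditions.

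A fourth objection is about size. The research hypothesis is framed against baseline, so change scores are a plausible reading of the Overview. At rho=0.7 the gain over change scores is 88.7 − 83.9, about 5 points, whereas over follow-up values alone it is 88.7 − 62.8, about 26. Quoting only the larger number would overstate the case. A narrowly selected healthy sample might also have a low rho on some scales; at 0.3 the gain over follow-up values alone is only about 3 points. Low rho does not favour change scores, however: there ANCOVA gains about 17 points over them (66 against 48.9).

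**Conclusion.** The point holds as one about precision. The Overview fixes an unadjusted between-group test although baseline values are meant to exist. Across the assumed range of rho, ANCOVA has higher power than either reading of that test: by about 3 to 26 points over follow-up values alone, and by about 17 down to 5 points over change scores as rho rises from 0.3 to 0.7. These sizes rest on an assumed rho, on an effect size borrowed from the imaging power statement, and on a single test at two-sided .05; they do not describe the voxel-wise analysis. The change is worth making before analysis, but the trial's validity does not depend on it.

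**What to change.** 1. **Reconcile the schedule first.** Bring Table 1 into line with the abstract and Secondary Outcome Measures so that a baseline assessment of each scale is actually scheduled. State whether controls have task fMRI on day 1, on which the Preparatory Phase and the abstract differ.
2. **Secondary scales.** In the Overview, make the between-group comparison of each scale at day 30 an ANCOVA of the follow-up value on arm and that scale's baseline value. Report the adjusted mean difference with a 95% CI, and keep the Mann-Whitney test as a sensitivity analysis. Age and sex may be added, since the design paragraph under Interventions describes the groups as matched on them.
3. **Extracted regional or network fMRI measures at day 14.** Include the day-1 pre-procedure value in the group-level linear model wherever both arms have that scan.

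**Cost.** One or two sentences in the analysis section plus the schedule corrections, with no added participants. The statistical price is 1 degree of freedom for the baseline term (about 2% in variance), or 3 with age and sex (57/54, about 6%). If rho were below about 0.13, the baseline term would lose slightly instead of gaining.

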##### fMRI Data Analysis

The fMRI data will undergo preprocessing using either the Data Processing and Analysis for Brain Imaging or CONN toolboxes, which will encompass essential steps such as slice timing correction, realignment for motion correction, regression to remove confounding effects, normalization to a standard template, smoothing to enhance signal-to-noise ratio, detrending to remove low-frequency drifts, and filtering to focus on relevant frequency bands, aligning with established practices in the field. After data preprocessing, amplitude of low-frequency fluctuation, functional connectivity, and large-scale functional brain network analysis will be conducted to investigate the difference in neurophysiological responses between the groups. The results will be interpreted in the context of the experimental paradigm to elucidate neural correlates of the studied phenomena, providing insights into the effects of *nasya karma* on brain function. Voxels exhibiting expected time-course correlations (30-second periods) will receive high activation scores, whereas those showing no correlation or deactivation will receive lower or negative scores, respectively. MRI data analysis will use general linear models via statistical parametric mapping (SPM). fMRI data will be processed using MATLAB 2023 (MathWorks Inc).

Resting phase MRI data will be analyzed using software tools such as SPM, the CONN toolbox, and the Functional Magnetic Resonance Imaging of the Brain Software Library (Analysis Group), whereas task phase fMRI will specifically use SPM. Given the focus on group data in this study, complex patterns of brain activation will be interpreted collectively rather than individually. For voxel-based analysis, a significance threshold of *P*<.01 at the voxel level and *P*<.05 corrected for false discovery rate (FDR) at the cluster level will be applied. Connectome-based analysis will use a threshold of *P*<.05 corrected for FDR. Additionally, Pearson correlation analysis will be performed to explore potential associations between clinical outcomes and fMRI findings, examining changes in brain activity following different interventions.

